### Weekly screening of progression and falls

Scheduled screening of progression in training will be used to indicate the capacity to continue to progress. The patients, who complete all the settings with good and high quality performance in 10 RM, will be able to progress to the next week. Those patients who will not show a good quality of performance will receive additional guidance on the exercises and will receive special attention from the orientation physiotherapist in terms of how to perform the exercises correctly. Thereby, if these patients complete all the parts with good and high quality of performance in 10 RM, they will be able to progress to the next week (Additional file 2: Table S2 and Additional file 3: Table S3).

### Screening of progression and falls

The number of falls will be noted by the physiotherapist at the hospital and by the patient at home. Weekly questionnaires will be used to follow up on any falls.

### Statistical analysis

Baseline values of the demographic characteristics and primary and secondary outcome measures of the participants in the MT, CG and the BRT will be compared using an unpaired *t*-test.

The Lilliefors and Levene tests will be used to examine the normality and homogeneity of variance for the primary and secondary outcome measures.

The participants’ performance in the training will be analyzed by three repeated-measures analyses of variance (RM-ANOVA), one for each part of the training (i.e., part 1, part 2 and part 3, with the training session as the within-group factor.

The training effects for each primary and secondary outcome measure will be analyzed for the three training conditions (i.e., control, motor and experimental) at the four assessment time points (i.e., Before the Training (BT), After the Training (AT), Follow up 1 and Follow up 2) using a mixed-design ANOVA with training as the between-group factor and the assessment time point as the within-group factor.

The effect sizes (ES) will be calculated for all comparisons at alpha = 0.05. A Tukey HSD post-hoc test will be used for multiple comparisons. The statistical software Statistica 11 from StatSoft (United States of America (USA)) will be used for all analyses, and p-values below 5 % will be considered to be statistically significant.

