# Randomized controlled trial protocol: balance training with rhythmical cues to improve and maintain balance control in Parkinson’s disease

**DOI:** 10.1186/s12883-015-0418-x

**Published:** 2015-09-07

**Keywords:** Randomized clinical trial, Parkinson’s disease, Physical therapy, Balance training, Postural control, Cues

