### Design and procedures

First, we defined the training guidelines and its progression. Subsequently, we developed an exercise program specifically to promote balance (active global exercises and rhythmical auditory cues, generated by a metronome). Subjects were randomly distributed among three groups. The first experimental group will be led by a physiotherapist, it will receive motor skill training with rhythmical auditory cues marked by a metronome (GBRT); the second experimental group will receive the same training without rhythmical cues (MT); and the control group (CT) will receive exercises in general orientation only with a general orientation. To verify retention after the training, subjects will be assessed and reassessed as a follow up 4 and 30 weeks after the end of their training (Fig. 1). The patients will be diagnosed by neurologists in the Movement Disorders Ambulatory Clinic of the University of São Paulo Faculty of Medicine Clinics Hospital (MD HC FMUSP). Physiotherapists will recruit patients on the database of the MD HC FMUSP and Motor-Sensory Learning Laboratory. They will conduct a brief telephone interview based on questions about their personal and medical history and self-perceived balance performance. Then, on a first visit, the subjects will be informed about the procedure and they will sign a consensual form.

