### Sample size calculation

The sample size calculation was based on the Mini-Balance Evaluation Systems Test (Mini-BESTest) score. The mean adopted—based on a pilot study of PD patients with similar characteristics to those of the patients in this trial—was 27, and indicated a 3-point difference between motor training and rhythmical auditory cues training. Based on this difference, the sample size calculation revealed that 150 patients (50 per group) would be sufficient for a power greater than 90 % (α = 0.05).

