### Outcome measures and test procedure

The primary outcome is balance, which will be assessed by the Berg Balance Scale (BBS) [38], postural stress test (PST) [39], push and release test (PRT) [40] and Mini BESTest (MBESTest) [41]. The secondary outcome is gait, which will be evaluated by the timed up and go test (TUG) [42] and by the freezing of gait, using the Freezing of Gait Questionnaire [43]. Independence in activities of daily living (ADLs), and motor performance will be assessed by the unified Parkinson’s disease rating scale (UPDRS) [44]. Falls and fear of falling will be evaluated during a variety of everyday activities and measured by the Falls Efficacy Scale-International (FES-I) [45].

The number of falls will be registered by the physiotherapist at the hospital and by the patient at home. A weekly follow-up of falling will be conducted.

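### No visit or contrast is fixed as deciding: the sized BRT-MT difference and the primary outcome carry no time point, the Tukey family is open, and no test is tied to 'improve' or 'maintain'

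*Protocol article*

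**What the plan says.** - **Title:** two claims are announced, "balance training with rhythmical cues to improve and maintain balance control".
- **Sample size calculation:** a pilot study "indicated a 3-point difference between motor training and rhythmical auditory cues training" on the Mini-BESTest. From this the section derives 50 per group for power above 90 % at alpha 0.05. It gives no visit and no SD.
- **Outcome measures and test procedure:** the primary outcome is balance, measured on four scales. No time point is named.
- **Design and procedures:** the later visits have a stated purpose, in a sentence that starts: "To verify retention after the training, subjects will be assessed and reassessed as a follow up 4 and 30 weeks after the end of their".
- **Statistical analysis:** each outcome is analysed "at the four assessment time points (i.e., Before the Training (BT), After the Training (AT), Follow up 1 and Follow up 2". The model is a mixed ANOVA in which arm varies between patients and visit varies within them. For the post-hoc step the section says: "A Tukey HSD post-hoc test will be used for multiple comparisons". Its significance rule is that "p-values below 5 % will be considered to be statistically significant". The section does not say which ANOVA term or contrast is decisive, whether Tukey runs within a visit or over all arm-by-visit means, or whether a significant F-test must come first.

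**The concern.** With five weeks of training, the three post-training assessments fall at about weeks 5, 9 and 35. 'Improve' belongs to the first and 'maintain' to the later two, and they can disagree: a gain at week 5 may be gone by week 35, or a difference may appear only at week 9. The plan does not say which pattern makes the trial positive. The same data could then be reported as positive or negative according to the visit chosen after the results are seen, and a lone late difference could be presented as maintenance without a shown gain at the end of training.

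This is separate from the number of balance scales. It remains if the Mini-BESTest is the only primary measure.

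**Working it through.** **1. Is a deciding visit stated or implied?** Sample size calculation, Outcome measures and Statistical analysis name none. Participants speaks of examining patients before and after training, which points to the end-of-training visit. The Discussion calls the long-term follow-up very important, which points the other way. The article does not settle the question.

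**2. The plan's own sample size.** Inputs from the article: difference 3, n = 50 per arm, alpha 0.05 (two-sided assumed). The SD is not given. Power = Φ(3 / (SD × √(2/50)) − c), with √(2/50) = 0.2 and c = 1.96.
- SD 4.0: 3/0.8 = 3.75; Φ(1.79) = 96 %.
- SD 4.5: 3/0.9 = 3.33; Φ(1.37) = 91.5 %.
- The largest SD that gives 90 % is 3 / (0.2 × (1.96 + 1.28)) = 4.63.

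The stated power can be neither confirmed nor refuted. It fits a single 5 % contrast if the SD is at most about 4.6.

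**3. False-positive risk over the three post-training visits, one scale.** I simulated 60,000 trials per setting with no true arm effect: 3 arms × 50, 4 visits, equal correlation between visits (assumed; the article gives none). Tukey critical values as t: 3.348/√2 = 2.37 for 3 means, 4.640/√2 = 3.28 for 12 means. The 12-mean version uses the pooled single-visit variance as error.

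| Reading of the plan | corr. 0.3 | 0.5 | 0.7 | 0.9 |
|---|---|---|---|---|
| Tukey per visit, no gate, any arm pair | 13.6 % | 12.6 % | 11.1 % | 8.5 % |
| Tukey per visit, no gate, BRT-MT only | 5.4 % | 4.9 % | 4.4 % | 3.4 % |
| Tukey per visit after a significant main-effect or interaction F, any pair | 5.7 % | 5.6 % | 5.5 % | 5.2 % |
| Tukey over all 12 cells, any pair | 0.9 % | 1.0 % | 0.8 % | 0.7 % |

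**4. Power under the strictest reading.** Same formula as step 2, with c = 3.28.
- SD 4.0: Φ(3.75 − 3.28) = Φ(0.47) = 68 %.
- SD 4.5: Φ(3.33 − 3.28) = Φ(0.05) = 52 %.
- 90 % power would need an SD of at most 3 / (0.2 × (3.28 + 1.28)) = 3.29.

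**5. Fixed order.** If BRT-MT is tested at After the Training at 5 %, and each follow-up only after success at the visit before it, a false claim with no true effect requires a false rejection at the first visit. The risk for that contrast on one scale is therefore 5 %. The simulation gave 4.9 to 5.1 %.

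**The case against.** The strongest reply has three parts.

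- **Multiplicity.** The plan does not run an unadjusted 5 % test at each visit. It fits one ANOVA per outcome and names Tukey HSD. For BRT-MT, the contrast on which the trial is sized, even ungated per-visit Tukey keeps the risk near or below 5 %. A post-hoc test is commonly read as following a significant F, and the risk is then 5 to 6 % for any pair. This stands. A reader might infer that the plan carries a 9-14 % error rate, or about twice the nominal level. The text does not support that as a general statement. It is an upper scenario that needs per-visit Tukey, no gate, and any arm pair counting, including MT versus control. Counting either the main effect or the interaction as success would also give about 10 %, but that comes from having two F-tests, not three visits.
- **'Improve' and 'maintain' are separated.** Design and procedures assigns the 4- and 30-week visits to retention, and retention presupposes a gain. This stands for purpose, so it would be too strong to say that the article confuses the two. What is missing is the link from purpose to test.
- **Detail for an SAP.** Testing order and Tukey family are often left to a document that is not shown here. This has weight. But the article does fix the sizing contrast, model, post-hoc test and significance rule, and as fixed they let any visit count. The visit at which 3 points are expected belongs with the sample-size statement.

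**Conclusion.** The point holds in limited form. No visit or contrast is fixed as deciding, and no test is tied to either claim in the title. The consequence is an undetermined error rate, not a known inflation. For one scale it lies anywhere from about 1 % to about 14 %, depending on the Tukey family, the gate and the arm pairs that count. The lower figures cannot be credited to the plan, because the choices that produce them are not stated. The strictest choice controls error but does not match the alpha of 0.05 used for sizing: power for 3 points would fall to about 68-52 % at SDs of 4.0-4.5.

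These figures assume equal between-visit correlation of 0.3 to 0.9, two-sided tests, complete data at 50 per arm, and the SDs named. The article gives neither the correlation nor the SD.

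**What to change.** In Sample size calculation and Statistical analysis, state that:

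1. the deciding contrast is BRT versus MT at After the Training, tested at 5 %;
2. the same contrast is then tested at Follow up 1 and after that at Follow up 2, each at 5 % and only if the visit before it was significant;
3. 'improves' rests on After the Training, and 'maintains' is claimed only if the sequence is significant through Follow up 2;
4. all other arm-by-visit comparisons are supportive.

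For that contrast on one scale, this holds the error over the three visits at 5 % without splitting alpha, and it matches the single 5 % contrast used for sizing. The cost is a few sentences and no extra patients. The downside is that a difference seen only at a follow-up visit can no longer be claimed as confirmatory.

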### The program

The exercise program aimed at improving balance is of 5 weeks’ duration with two sessions a week, 45 min per session, and consists of general physiotherapy exercises. Each session will be divided into five warm-up minutes—30 min for the main part and 10 min for the cool down. General exercises will be taught in each part of the therapy [46, 47], as well as balance improvement exercises, which will be defined according to the program guidelines. The training sessions will be in groups comprising 10 participants and 2 physiotherapists. The physical therapists will place themselves behind the patients so that they can catch or hold the patients if they fall.

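### The four-visit mixed-design ANOVA is by default a complete-case analysis that assumes sphericity, so late loss would also thin the end-of-training comparison

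*Protocol article*

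**What the plan says.** The Statistical analysis section of the protocol article sets one model for each primary and secondary outcome, comparing the three arms. The model is specified in these words: "using a mixed-design ANOVA with training as the between-group factor and the assessment time point as the within-group factor". It is fitted to data from every planned visit, which the section gives as "at the four assessment time points (i.e., Before the Training (BT), After the Training (AT), Follow up 1 and Follow up 2"). For pairwise work, "A Tukey HSD post-hoc test will be used for multiple comparisons". The assumption checks are also named: "The Lilliefors and Levene tests will be used to examine the normality and homogeneity of variance" of the outcome measures. Statistica 11 is given as the software for all analyses.

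The visit times come from two other sections. Under The program, "The exercise program aimed at improving balance is of 5 weeks’ duration with two sessions a week", which puts the after-training assessment at week 5. Under Design and procedures, "subjects will be assessed and reassessed as a follow up 4 and 30 weeks after the end of their training", which gives weeks 9 and 35.

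The Sample size calculation section says that "150 patients (50 per group) would be sufficient for a power greater than 90 % (α = 0.05"), for a 3-point Mini-BESTest difference between motor training and cued training. The article gives no SD, no within-patient correlation and no dropout rate.

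**The concern.** Two properties of the named model matter here.

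**Complete cases.** With time as a within-subject factor, a classical mixed-design ANOVA needs a full set of four values per person. Someone who trains, is assessed at weeks 5 and 9 and then misses week 35 contributes nothing to the model, although their end-of-training value was collected. The longest gap, 26 weeks, comes just before the last visit. Participants have a history of falls and a progressive disease, and the control arm receives orientation only. Late absence related to balance or to arm is therefore plausible. If it occurs, the week-5 comparison is made among people selected by what happened months later.

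**Sphericity.** The univariate F-tests for time and for training by time assume that the differences between any two visits have the same variance. Visits 4 weeks apart are likely to agree more closely than visits 26 weeks apart. Lilliefors addresses normality and Levene addresses equality of variance between groups, so neither examines this assumption. Tukey comparisons that use the pooled within-subject error would rest on it too.

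**Working it through.** **1. Visit times.** Training lasts 5 weeks, so the assessments fall at 0, 5, 5 + 4 = 9 and 5 + 30 = 35 weeks. The gaps are 5, 4 and 26 weeks.

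**2. The plan's own figure.** Without an SD, 50 per group cannot be reproduced, but the SD it implies can be found. By the normal approximation (two-sided alpha 0.05 assumed), the largest SD that gives 90% power is 3 × √(50/2) / (1.960 + 1.282) = 15 / 3.242 = 4.63. By the two-sample t-test it is about 4.58. At 50 per group, t-test power is 96% for SD 4.0, 91% for SD 4.5 and 84% for SD 5.0. The stated power is attainable but cannot be verified.

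**3. Late loss.** Assume that everyone attends week 5 and a fraction *d* is lost before week 35. The ANOVA then uses 50 × (1 − *d*) per arm at every visit. An available-data analysis would still have 50 per arm at week 5. Power below is for a two-sample t-test of a 3-point difference.

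| Late loss (assumed) | Per arm in the ANOVA | All arms | Power, SD 4.0 | Power, SD 4.58 |
|---|---|---|---|---|
| 0% | 50 | 150 | 96% | 90% |
| 10% | 45 | 135 | 94% | 87% |
| 20% | 40 | 120 | 91% | 82% |
| 30% | 35 | 105 | 87% | 77% |

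Both SDs are assumptions. The value 4.58 is solved backwards from 90% power, so it leaves no margin. A t-test stands in for the planned model, so these figures only illustrate the cost.

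**4. Sphericity.** The 3 × 4 interaction F-test was simulated with no true effects, 50 per arm and complete data at weeks 0, 5, 9 and 35 (20,000 trials per setting, nominal 5%). Epsilon is 1 when sphericity holds and at worst 1/3 with four visits. All covariance structures are assumed.

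| Covariance | Epsilon | Uncorrected | Greenhouse-Geisser |
|---|---|---|---|
| Compound symmetry | 1.00 | 5.1% | 4.9% |
| Random slope, mild | 0.98 | 4.9% | 4.6% |
| Random slope, stronger | 0.82 | 6.5% | 5.1% |
| Constant 0.5 plus a decaying part | 0.83 to 0.56 | 6.1% to 9.1% | 4.9% to 5.1% |
| Exponential decay, half-life 5 to 200 weeks | 0.83 to 0.52 | 6.6% to 9.5% | 4.8% to 5.3% |

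Uncorrected, the test is close to nominal when sphericity nearly holds, and rejects in roughly 6-9% of null trials when correlation decays with time. The correction restores about 5% in every setting.

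**The case against.** The source is a condensed article, and a full protocol or analysis plan may contain a sphericity correction, an imputation rule or definitions of the analysis sets. That is a fair point. Silence on these is not a decision to do without them, and their absence is not the finding. What the article does state is the model itself, and both properties follow from that choice.

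A reader might infer that the interaction test is anti-conservative outright. The documents do not support that. They give no covariance, and unequal spacing makes non-sphericity plausible without proving it. Under compound symmetry or a mild random slope the size is about 5%.

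A reader might also infer that the comparison will lose the protection of randomisation. No attrition figures are given, by arm or by balance, so the most that can be said is that it may. The baseline comparisons are separate tests and are not affected by this model's deletion of incomplete cases.

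The power loss can also be read too strongly. At SD 4.0, power is still 91% after 20% late loss. Assuming independent misses at all three later visits would give a larger loss (0.90³ = 0.73 complete at 10% per visit). Part of that, however, is week-5 data that nobody would have, so it does not measure what late loss costs the week-5 contrast.

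Finally, sphericity alone could be handled by a Greenhouse-Geisser correction without changing the model. That is true, but the correction does not bring back the deleted patients.

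**Conclusion.** The point holds in conditional form. The named analysis, unless values are imputed, makes the week-5 comparison depend on attendance at week 35. That follows from the stated method and visit schedule and needs no assumed figure. Its size does need one: at assumed late loss of 10% to 30%, 5 to 15 of 50 patients per arm would drop out of a comparison for which their data exist. Power would be about 87% to 77% if the SD were 4.58, and higher if it is smaller. Bias is possible but is not shown.

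The sphericity part is weaker. If the assumption fails and nothing corrects for it, the interaction test would run at roughly 6-9% under the decaying correlations tried. The article neither shows that the assumption fails nor rules out a correction.

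The change is worth making because one substitution deals with both parts.

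**What to change.** Replace the mixed-design ANOVA, for each outcome to which it is applied, with a likelihood-based mixed model for repeated measures. It should use all available visits of all randomised participants in their allocated arm, with categorical visit, arm-by-visit terms, baseline adjustment and an unstructured covariance. State the end-of-training and follow-up contrasts to be taken from it. A patient lost after week 5 then still informs the week-5 contrast, and sphericity is not assumed.

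The model assumes that data are missing at random. If absence depends on unobserved worsening, bias can remain. Add one sensitivity analysis for data not missing at random, for example one that assumes worse balance after loss.

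The cost is changed analysis wording and possibly other software than Statistica 11. No new data or visits are needed. The article describes the study as ongoing in stage 1. If the outcome data have not yet been examined by arm, the change can still be prespecified.

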## Discussion

Even with the ideal medical treatment, PD patients still present problems with functional activities, gait and balance [2]. To minimize these deficits, physiotherapy is prescribed as a coadjuvant to drug treatment, being more effective when integrated with specific training linked to sensorial cues and cognitive strategies [16–18, 20, 21].

Physiotherapy exercises lead to improved performance in PD patients, as shown in the literature [22, 28].

As physiotherapy has a highly beneficial effect on balance [24], there is some distinction among compensatory mechanisms that could be useful in gait and balance therapeutic intervention. Therefore, our hypothesis is that rhythmical cues associated with exercises and motor training can facilitate an anticipatory and compensatory reaction [27, 28], improving gait and preventing falls, in the following ways: 1) by increasing attentional engagement, thus promoting an improvement in performance [19]; 2) by increasing sensory-motor integration through thalamic activation of subcortical structures from the internal globus pallidus and cerebellum [32]; and 3) by stimulating internal signals from the basal nucleus, facilitating previously learned movements [34].

The exercises and motor training proposed in this study may improve the performance of balance-related activities in PD. The long-term effects of the exercises and motor training in this population are not clear [25]; however, the precocious and regular physiotherapeutic intervention in PD preserves and improves motor function [15], which suggests a neuroprotective effect [19]. The disease is progressive and the motor training and exercises should be adapted to the patient’s needs and PD progression [16].

It is likely that PD patients diagnosed by neurologists in the Movement Disorders Ambulatory Clinic of the University of São Paulo Faculty of Medicine Clinics Hospital, H&Y stage II–III, will be able to learn how to use the compensatory mechanisms necessary to improve postural instability. The inclusion of rhythmical auditory cues in the motor program may help to improve balance in this group of PD patients [26]. We intend to promote strong evidences that this training program may be more effective than others and will be save compensatory and anticipatory reactions at the exact moment that a response is necessary to prevent a fall. Application and progression of the motor program may promote improvement in automatic postural responses. Such responses are influenced by cortical processing related to learning, previous experiences and initial postural conditions [5].

The cues mostly influenced temporal aspects, facilitating sensory-motor integration, as suggested by previous studies [19]. Therefore, auditory cues may facilitate anticipatory responses sufficiently early to avoid loss of balance in the same way that they may promote compensatory responses. The compensatory adjustments depend on detection of the imbalance through different sensorial modalities [6–9]. A possible explanation for this mechanism of action is that, under challenging conditions, PD individuals prioritize voluntary tasks over postural control [11]. In addition, rhythmical cues may increase attentional control, serving as dual-task training.

We suggest that BRT may facilitate attentional engagement with the tasks. External cue stimulation of the sensorial systems may be a good strategy for improving sensorial integration and compensating for basal nucleus deficits. One explanation for the transfer of the benefits of exercise may pertain to the repair or consolidation of overlapping motor circuitry involved in cognitive and automatic components of movements [19]. In fact, there are many cognitive aspects that may assist with the generalization and maintenance of BRT, which can then be applied to activities of daily living.

We suggest that balance training should be started early, as falls occur clinically when the patient has already exhausted all compensatory resources used by the nervous system, which is compromised by basal ganglia deficits, and when postural and cognitive responses are no longer effective [27, 28]. The long-term follow up in the proposed study will be very important to verify important questions concerning the potential effects of, and limitations of, balance training. Our belief is that this trial will provide evidences about the effectiveness of rhythmical cues on balance in PD patients, providing a therapeutic strategy that can be used to treat such dysfunctions.

The physiotherapy proposed to improve balance in individuals with PD is effective, low-cost, and easy to apply. This study contributes to the subject knowledge, with specific knowledge about balance in PD patients and the mechanisms involved in motor control. It also provides data about functional diagnosis, prognosis, clinical programs, and the management of balance treatment programs. This program may also be allied to different sorts of parkinsonisms and other motor disorders that influence balance.

